#### Secondary

To evaluate the value of using both mpMRI and CEUS + CUDI for targeted prostate biopsies.

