Limited data is available for the value of CEUS-targeted cores. Van Hove et al. reviewed 6 studies that compared the CDRs for CEUS-targeted biopsies and systematic biopsies [9]. They report that targeted biopsy cores achieved CDRs between 13% absolute lower and 4% absolute higher than systematic cores in these heterogeneous studies with mixed patient groups and various CEUS variants used. None of the studies in this review have included the use of quantitative techniques. A previous study done in our own institution, that retrospectively correlated CEUS imaging with and without quantification with systematic biopsy results, showed improved significant PCa detection with the use of quantification. In 82 patients, 5.6% of biopsy locations that were classified benign on imaging showed clinically significant disease when quantification software was used, compared to 8.5% for CEUS without quantification [20]. Unfortunately, no targeted biopsies were taken in this retrospective analysis. We hypothesize that the use of CUDI quantification software in our current study will result in a CDR for significant disease up to the level of systematic biopsies or better. To our knowledge, there are no published data on the complementarity of mpMRI and CEUS in prostate cancer detection and biopsy targeting. Based on the available data on the separate techniques, we expect that the combination will result in a CDR higher than that of systematic biopsies, especially for the detection of clinically significant disease.

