### Study design

This study is a prospective in-vivo study in humans in which we perform MRI imaging and CEUS imaging in biopsy-naïve patients scheduled for prostate biopsies. Targeted prostate biopsies based on these images will be taken besides current standard of care systematic biopsies. Since both imaging modalities and targeted biopsies will be performed in the same patients, every patient effectively serves as his own control. Patients will undergo mpMRI imaging and CEUS imaging approximately 1 week before the scheduled biopsy appointment. During this week, MRI reading will be performed by a specialized uroradiologist with approximately 10 years of prostate mpMRI experience using the European Society of Urogenital Radiology (ESUR) Prostate Imaging Reporting and Data System standardised scoring system, version 2 (PIRADS v2) [21]. The radiologist is blinded to CEUS and CUDI results. The CEUS recordings will be analysed using the CUDI quantification technique. An observer experienced in CEUS of the prostate will read the CEUS recordings and CUDI-maps, while blinded to the MRI results. Before the biopsy procedure, the MRI - based biopsy targets and CEUS + CUDI - based biopsy targets are therefore predetermined independently from each other. During the biopsy session, approximately 1 week after the imaging is recorded, a physician who is blinded to all imaging results and the targeted biopsy procedure will first perform the standard 12-core systematic biopsy to prevent potential bias by post-biopsy haemorrhage seen on ultrasound after targeted biopsies. Then a separate observer, using an MRI-US fusion device, takes a maximum of 4 targeted biopsies from the MRI lesions delineated by the radiologist followed by a maximum of 4 targeted cores from the CEUS + CUDI lesions identified by the CEUS expert. Per-patient CDRs and tumor differentiation grades are compared between each of the biopsy regimens: MRI - targeted biopsies, CEUS + CUDI - targeted biopsies and systematic biopsies.

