### Sample size and statistical analysis

#### Statistical analysis

The per-patient PCa detection rates of both targeted biopsy regimens will be tested separately for non-inferiority against current standard 12-core systematic biopsies using a one sided non-inferiority test for correlated proportions [22, 23]. To evaluate if image- targeted biopsies can be used complementarily, we will also perform the same comparative analysis for the targeted biopsy results combined, compared to the systematic biopsies. Moreover, the per-patient CDR’s of all three biopsy protocols will be directly compared using McNemars test for correlated proportions. The same analyses will be performed including all tumors and including clinically significant tumors only, defined as PCa with a Gleason score ≥3 + 4 = 7.

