#### Sample size calculation

The sample size calculation is based on the non-inferiority test between the targeted biopsy procedures and the systematic biopsies. For this test we performed a power analysis, with the detection rate for systematic biopsies set at 45% [24], a power of 80% and the significance level (alpha) of 5%. The maximum allowable difference in detection rate for the targeted biopsies to be considered non-inferior to systematic biopsies was set at 1%. We expect a maximum proportion of discordant pairs of 15% and a detection rate difference of 5%. The required sample size according to these specifications is 260 patients. Based on the estimation that 15% of the patients that are scheduled for biopsies will not receive targeted biopsies due to the absence of PCa suspected lesions on imaging; a total number of 299 patients will be enrolled in the study.

Literature shows that of all positive biopsies about 25% is Gleason >6 [25–27]. Results from our institution differ from literature as only 40% of all the patients with PCa at biopsy have a Gleason score 6 PCa, while 60% of them have a Gleason score >6 PCa. Thus, numbers of positive biopsies and Gleason score > 6 are higher than reported in literature. Based on our historical data we expect that by including 299 patients in the study we will find ~65 cases with a Gleason score = 6 and ~100 cases with a Gleason score > 6. For differentiation between Gleason score we hypothesize that we need at least 40 people in both Gleason grade groups.

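### Combined MRI + CEUS targeting is expected to detect more cancer than systematic biopsy, but the only test assigned to that comparison is non-inferiority; no superiority step is pre-specified

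*Protocol article*

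**What the plan says.** In Expected outcomes, after noting that no data exist on how the two imaging methods complement each other, the article states "we expect that the combination will result in a CDR higher than that of systematic biopsies". It adds that the gain should be clearest for clinically significant disease. It gives no size for the gain. The secondary objective is worded more neutrally: "To evaluate the value of using both mpMRI and CEUS + CUDI for targeted prostate biopsies".

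The Statistical analysis section proceeds in this order:

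1. Each targeted regimen is tested separately against systematic biopsy "using a one sided non-inferiority test for correlated proportions".
2. To judge whether the two kinds of targeting complement each other, "we will also perform the same comparative analysis for the targeted biopsy results combined, compared to the systematic biopsies".
3. In addition, "the per-patient CDR’s of all three biopsy protocols will be directly compared using McNemars test for correlated proportions".
4. All of this is done for all tumours and again for Gleason 7 or higher.

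The Study design section lists the regimens to be compared: "MRI - targeted biopsies, CEUS + CUDI - targeted biopsies and systematic biopsies". The combination is not on that list.

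The Sample size calculation section sets a 1-point margin, an expected 5-point difference, at most 15% discordant pairs, 80% power and 5% alpha. This gives 260 men, raised to 299. No separate figures are given for the combination.

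**The concern.** The expectation for the combination is directional: it should find more cancer. The test assigned to it asks only whether it is worse by more than 1 point. The single regimens get both a non-inferiority test and a test of difference. The combination, the regimen for which a higher overall detection rate is stated outright, gets only the first. The same holds in the Gleason 7 or higher analysis, where the gain is expected most.

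At stake is what may be concluded on the trial's one secondary objective. Followed as written, the planned success criterion supports only the statement that the combination is not more than 1 point worse. A claim of higher detection would rest on a reading of the data that the article does not set out in advance.

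**Working it through.** **Which test applies to the combination.** When the text refers to the same comparative analysis, only the non-inferiority test has been introduced. McNemar's test comes in the next sentence as an addition and is assigned to three protocols. Study design identifies these as MRI-targeted, CEUS + CUDI-targeted and systematic. On the natural reading, no test with equality as its null hypothesis is assigned to combined versus systematic.

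**Reproducing the plan's figure.** With discordance ψ = 0.15, difference d = +0.05, margin m = 0.01 and one-sided 5% alpha:

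n = (1.645 + 0.842)² × ψ / (d + m)² = 6.183 × 0.15 / 0.0036 = 257.6, so 258.

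Using ψ - d² as the variance in whole or in part gives 254 to 257. All are close to the stated 260. Two-sided alpha gives 322 to 328 and does not fit. So 260 is a one-sided non-inferiority size that assumes a true 5-point advantage. The step to 299 is 260 × 1.15.

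**How far apart the two claims lie.** Assumption: the 15% discordance also holds for the combination. At n = 299 this is 0.15 × 299 = 44.85, so 45 discordant pairs. With an odd number of pairs the excess x (combined-only minus systematic-only) must be odd. SE = √(45 - x²/299) / 299.

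- Non-inferiority, x = 7: d = 0.0234, SE = 0.0224, z = (0.0234 + 0.01)/0.0224 = 1.49. Fails against 1.645.
- Non-inferiority, x = 9: d = 0.0301, SE = 0.0224, z = 0.0401/0.0224 = 1.79. Passes. The matching one-sided 95% bound is 0.0301 - 1.645 × 0.0224 = -0.007, or -0.7 points. It is inside the margin but below zero.
- Superiority (McNemar, two-sided 5%), x = 13: 13/√45 = 1.94. Fails against 1.96.
- Superiority, x = 15: 15/√45 = 2.24. Passes, at 15/299 = +5.0 points.

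At n = 260 with 39 discordant pairs, non-inferiority first passes at 9 men (+3.5 points) and superiority at 13 men (13/√39 = 2.08; +5.0 points).

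**Power of the missing superiority test.** Power = Φ[(√n × d - 1.96 × √ψ) / √(ψ - d²)].

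With the plan's own d = 0.05 and ψ = 0.15 at n = 299: (17.29 × 0.05 - 1.96 × 0.3873) / √0.1475 = 0.1055 / 0.3841 = 0.275, so power is 61%. At n = 260 it is 55%. For 80% power, 469 men would be needed two-sided, or 369 one-sided.

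The documents give neither a difference nor a discordance for the combination. The range over assumed values (two-sided 5%) is:

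| Difference | Discordance | Power, n = 260 | Power, n = 299 |
|---|---|---|---|
| 5 points | 15% | 55% | 61% |
| 5 points | 30% | 31% | 35% |
| 8 points | 15% | 92% | 95% |
| 8 points | 30% | 66% | 72% |
| 10 points | 15% | 99% | 99% |
| 10 points | 30% | 84% | 89% |

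**The case against.** A reader might infer that a higher rate for the combination can never be confirmed in this trial. The documents do not support that. The paired difference estimated for the non-inferiority test also yields a confidence limit. If the lower limit lies above 0, superiority follows at no cost in type I error for that comparison. What is missing is the advance statement that this step will be taken and at what level.

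A reader might also treat the expectation as a formal superiority hypothesis. It is not one. It stands under Expected outcomes, and the objective behind it is only to evaluate the value of using both methods. Expecting a benefit while testing non-inferiority is no contradiction in itself, since the sample size calculation does exactly that with its 5-point difference and 1-point margin.

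A third tempting argument is that truly equal regimens would pass non-inferiority about 12% of the time (simulated at 15% discordance and n = 299). That is not an error rate: equal regimens are non-inferior, so those passes are correct. The figure shows only that a pass does not mean higher detection.

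The strongest remaining objection is that this is a condensed article, and a step from non-inferiority to superiority in a secondary analysis may well stand in the full protocol or analysis plan. That would answer a complaint about silence. Here, though, the article names a test for this comparison, names a different test for the others, and the named test does not match its own stated expectation. That mismatch stands. The objection does limit the weight of the point: it concerns a secondary analysis and leaves the primary comparisons and the sample size untouched.

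**Conclusion.** The point holds in a limited form. The combined regimen is expected to detect more cancer than systematic biopsy, but the article assigns that comparison only a one-sided non-inferiority test and pre-specifies no superiority step. A non-inferiority pass alone would not support a claim of higher detection.

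In size, the gap between the two claims is 9 against 15 excess men out of 299, or +3.0 against +5.0 points. This rests on carrying the plan's 15% discordance over to the combination and on a two-sided 5% level for McNemar's test, which the article does not state. The trial could show superiority but is not sized for it at 80% under its own 5-point and 15% inputs. Over assumed differences of 5 to 10 points and discordance of 15% to 30%, two-sided power at 260 men runs from about 31% to 99%.

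**What to change.** In the Statistical analysis section, add combined-targeted versus systematic to the McNemar comparisons, for all cancers and for Gleason 7 or higher. State the order: first the non-inferiority test against the 1-point margin and, only if it passes, the same paired difference against 0 at two-sided 5%. Say that only the second step supports a claim of higher detection. Describe it as a secondary test not sized at 80%, and give its power with the assumed difference and discordance.

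The cost is a sentence or two and one more paired test on a 2×2 table that the non-inferiority test already needs. It requires no extra patients or procedures, and the fixed order adds no type I error for that comparison. The downside is that the claim of higher detection must then clear a stricter threshold, with modest stated power.

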#### Sample size calculation

The sample size calculation is based on the non-inferiority test between the targeted biopsy procedures and the systematic biopsies. For this test we performed a power analysis, with the detection rate for systematic biopsies set at 45% [24], a power of 80% and the significance level (alpha) of 5%. The maximum allowable difference in detection rate for the targeted biopsies to be considered non-inferior to systematic biopsies was set at 1%. We expect a maximum proportion of discordant pairs of 15% and a detection rate difference of 5%. The required sample size according to these specifications is 260 patients. Based on the estimation that 15% of the patients that are scheduled for biopsies will not receive targeted biopsies due to the absence of PCa suspected lesions on imaging; a total number of 299 patients will be enrolled in the study.

Literature shows that of all positive biopsies about 25% is Gleason >6 [25–27]. Results from our institution differ from literature as only 40% of all the patients with PCa at biopsy have a Gleason score 6 PCa, while 60% of them have a Gleason score >6 PCa. Thus, numbers of positive biopsies and Gleason score > 6 are higher than reported in literature. Based on our historical data we expect that by including 299 patients in the study we will find ~65 cases with a Gleason score = 6 and ~100 cases with a Gleason score > 6. For differentiation between Gleason score we hypothesize that we need at least 40 people in both Gleason grade groups.

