## Background

The incidence of PCa has increased in the 1990’s, due to increased awareness and prolific Prostate Specific Antigen (PSA) screening. Although in the United States this trend has partly reversed, PCa is still the most common cancer in men representing 21% of cancer cases and it is estimated that 180,890 men will be diagnosed with PCa in United States in 2016 [1]. In Europe the incidence has increased, with 417,00 new PCa diagnoses in 2012 [2]. According to current standards, patients with a clinical suspicion of PCa based on elevated serum PSA and/or digital rectal examination should undergo 10–12 systematic transrectal ultrasound (TRUS)-guided prostate biopsies to confirm the diagnosis [3]. These systematic “blind” prostate biopsies lead to a considerable rate of overdiagnosis of clinically insignificant PCa as well as underdiagnosis and undergrading of significant PCa [4]. Image - guided targeted biopsy approaches have been proposed to address these problems [5]. Prostate cancer imaging has thus far developed on two platforms: MRI and Ultrasound. On the MRI platform, multiparametric MRI(mpMRI) in which diffusion - weighted MRI and dynamic contrast- enhanced MRI sequences are added to anatomical T2-weighted imaging has become the standard for PCa imaging [6]. A 2015 systematic review on the accuracy of mpMRI for the detection of prostate cancer found 12 studies and reported a negative predictive value for the detection of clinically significant prostate cancer between 63 and 98% and positive predictive values of 34–68% [7]. However, these results should be interpreted with caution since several used biopsy pathology as the reference standard to calculate sensitivity and specificity. Several meta-analyses have addressed the value of mpMRI - targeted biopsy cores and these show an improved per-core detection rate and a beneficial increased per-patient detection rate in patients with a persistent clinical suspicion after prior negative biopsies [5, 8]. The 2016 update of the EAU (European Association of Urology) guidelines on PCa now recommends performing mpMRI in these patients. However, at this point, the value of using mpMRI and MRI-targeted biopsies at initial biopsy in biopsy-naïve patient is debated [3]. Even though high negative predictive values for detecting significant prostate cancer have been reported, significant disease can still be missed by MRI - targeted biopsy. Furthermore, considerable heterogeneity and risk of selection bias of published results exists. [8, 9]. The EAU guidelines therefore recommend combining systematic and targeted biopsies [3]. The review by Van Hove et al. shows a 1–43% absolute and 2–430% relative increase in per-patient detection rate can be achieved by adding mpMRI - targeted cores to systematic cores [9]. Several methods of using the information obtained by mpMRI to target the region of interest with prostate biopsies exist: in cognitive targeting, the operator makes a visual estimation of where the MRI lesion is located during a TRUS-guided biopsy procedure. Taking in-bore biopsies during MRI scanning reduces the risk of targeting error but due to its magnet time consuming and therefore costly nature, it is not used often. Fusion devices have been developed that register the MRI images and US together, guiding the observer towards the MRI lesion during the TRUS procedure [10, 11].

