## Discussion

Improvement of the PCa diagnostic pathway is necessary, and will likely depend on the advances in PCa imaging. Multiparametric MRI has a recognized value before a second biopsy in case of a persistent clinical suspicion for PCa. The value in biopsy - naïve patients and the possibility to omit systematic biopsies is debated [3]. Contrast -enhanced ultrasound has shown promising results, but should currently be viewed as experimental. This trial will provide data on both these techniques, allowing comparison and assessment of complementarity. The study design chosen is in line with recommendations formulated by the Standards of reporting for MRI-targeted biopsy studies (START) Working Group [33] and by van Hove et al [9]. To validate imaging - targeted prostate biopsy protocols van Hove et al. recommend using either one of two study designs: randomize patients to undergo either systematic biopsies alone or systematic biopsies and targeted biopsies. In the other option every patient undergoes both targeted biopsies and systematic biopsies by separate blinded observers. In our study design all patients undergo both imaging procedures and both targeted and systematic biopsies. The targeted biopsies and systematic biopsies are performed by separate observers. The targeted biopsy locations are predetermined by blinded readers and targeted through a fusion device. To prevent potential bias by post-biopsy haemorrhage seen on ultrasound the targeted biopsies are performed after the systematic biopsies. This way we prevent information gathered from one imaging technique to influence biopsy targeting for the other imaging technique. In both study designs the (significant) PCa detection rates are compared. An advantage of using these study designs is that there is no spectrum bias, i.e. the relevant biopsy population is being studied. Also, there is no observer bias, the investigator reading the images does not already know that there must be a tumor. Both spectrum bias and observer bias occur when translating results obtained from the correlation of imaging and radical prostatectomy specimens towards the primary diagnostic setting. Furthermore, the endpoint in this study design, (significant) PCa detection, is the most relevant endpoint in the clinic. We therefore believe that our trial will provide important and necessary data on one of the most relevant topics in PCa care. This data is gathered in a recommended, standardized fashion to minimize bias and allow data pooling.

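### The step from 260 to 299 treats men with no lesion on imaging as adding no pair; they are targeted-negative, and leaving them out could only shift discordant pairs in favour of targeted biopsy

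*Protocol article*

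**What the plan says.** The Sample size calculation section plans a paired non-inferiority test. The "detection rate for systematic biopsies set at 45"%, power is 80%, and the maximum allowable shortfall for targeted biopsies "to be considered non-inferior to systematic biopsies was set at 1"%. It assumes at most 15% discordant pairs and a 5-point difference in detection, and arrives at 260 men. It then enrols 299 because "15% of the patients that are scheduled for biopsies will not receive targeted biopsies due to the absence of PCa suspected lesions on imaging".

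The Statistical analysis section states: "The per-patient PCa detection rates of both targeted biopsy regimens will be tested separately for non-inferiority against current standard 12-core systematic biopsies". The test is one-sided and paired. The same comparison is planned for the two targeted regimens combined, and for clinically significant tumours only. The section does not say whether a man without a target counts as negative for that regimen or leaves the test.

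The Biopsy procedure section gives the 12-core systematic biopsy without exception. The Study design section describes each patient as his own control. The Discussion describes all patients as having both kinds of biopsy and adds: "An advantage of using these study designs is that there is no spectrum bias, i.e. the relevant biopsy population is being studied".

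**The concern.** A 15% allowance of this kind is what one adds for patients who cannot be evaluated. A man without a lesion on imaging can be evaluated. His systematic result is observed, and his result under a targeted-only regimen is known: no target, no cores, no cancer found. His pair is either negative on both or positive on systematic biopsy alone. It can never be positive on targeted biopsy alone.

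If such men are left out, every discordant pair that goes counts against targeted biopsy and no favourable pair can go. Concordant-negative pairs, which do not affect the numerator of the difference, go as well. The comparison would then concern men with a visible lesion, not the biopsy-naïve men named in the objective and population sections, and the Discussion's statement on spectrum bias would no longer hold. With a margin of only 1 point, a small shift can decide the result.

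The point also applies to each modality separately. A man with an MRI target and no CEUS target is CEUS-negative, not missing. If he were dropped from one test and kept in the other, the regimens would not be compared in the same men.

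**Working it through.** **Inputs from the protocol article (Sample size calculation and Statistical analysis).** Discordant proportion ψ = 0.15; difference d = +0.05, read as favouring targeted biopsy (cells 0.10 and 0.05); margin m = 0.01; one-sided test, with "the significance level (alpha) of 5"%; power 80%; share without a lesion 0.15. The 45% systematic rate is not needed once ψ and d are fixed.

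**Input not given.** s, the systematic detection rate in men without a target; assumed 0 to 30%.

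**1. The plan's own figures.** For the paired score test with restricted null variance v0 = 0.1532:

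n = [1.645·√v0 + 0.842·√(ψ − d²)]² / (d + m)² = [1.645·√0.1532 + 0.842·√0.1475]² / 0.06² = 259.8, so 260.

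This matches the stated figure and confirms a one-sided alpha of 5%; a one-sided 2.5% would need 322 to 331, depending on the variance formula. Then 260 x 1.15 = 299 exactly, so the allowance for men without a lesion is the only inflation applied. (Side point: 299 x 0.85 = 254 men would have a lesion. Division, 260/0.85, gives 306. The gap is minor.)

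**2. Effect of leaving these men out.** Let D be the whole-cohort difference, targeted minus systematic. Men without a target make up 0.15 of the cohort and contribute −0.15·s to D. The difference in the remaining men is

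D_kept = (D + 0.15·s) / 0.85.

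The bias is D_kept − D = 0.15·(D + s)/0.85. It equals the 1-point margin when D + s = 0.0567, that is at s = 6.7% if D = −1 point and s = 5.7% if D = 0.

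**3. False non-inferiority at the margin.** Simulated with n = 299, D = −0.01, 15% discordance among men with a lesion, and a one-sided 5% Wald paired test:

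| s | D_kept (points) | Men without a target left out | All men counted |
|---|---|---|---|
| 0% | −1.18 | 4% | 5% |
| 5% | −0.29 | 9% | 5% |
| 10% | +0.59 | 16% | 5% |
| 20% | +2.35 | 40% | 5% |
| 30% | +4.12 | 69% | 5% |

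With the score test and 15% discordance in the whole cohort instead, the left-out column is 4.3%, 8.6%, 15.6%, 41% and 76%. The pattern is the same; the size at high s depends on where the 15% discordance is placed.

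**4. Power at 299 when all men are counted.**

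- If ψ = 15% and d = +5 points describe the whole cohort: Φ(0.06·√299/√0.1475 − 1.645) = 85%, and 260 would have been enough.
- If they describe only men with a lesion: D = 0.85·0.05 − 0.15·s and ψ = 0.85·0.15 + 0.15·s.

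| s | D (points) | ψ | Power at 299 | Men needed for 80% (Wald) |
|---|---|---|---|---|
| 0% | +4.25 | 12.75% | 83% | 282 |
| 5% | +3.50 | 13.50% | 69% | 409 |
| 10% | +2.75 | 14.25% | 54% | 624 |
| 20% | +1.25 | 15.75% | 26% | 1922 |

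**The case against.** The strongest reply is that no exclusion is ordered. The Statistical analysis section names no analysis set, speaks of per-patient rates, and sits beside a design in which each man is his own control. The Sample size calculation section also counts its expected cancers (about 65 and about 100) over all 299 men. This stands: a reader might infer that the plan commits itself to a biased test, but the exclusion is implied by the 299 and not stated as an analysis rule.

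Nor does the inflation strictly prove exclusion. If the planning values describe men with a lesion, a whole-cohort analysis also needs more than 260, and at s = 0 it needs 282. That reading holds the planned power only for s near zero, since power is already 69% at s = 5%. It is also not the reason the article gives.

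Three stronger readings should be resisted.

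- One might say that only unfavourable pairs are removed. In fact most would be concordant-negative (90% of them at s = 10%); the statement is true of the discordant pairs alone.
- One might say that the bias exceeds the margin. That holds only above s of roughly 6 to 7%, and s is not in the document.
- One might take s from the Background, where a review "reported a negative predictive value for the detection of clinically significant prostate cancer between 63 and 98"%. That range is for MRI alone and for significant cancer, and the article itself urges caution with it. The 15% is for lesions on imaging without naming a modality, and the sample size uses an all-cancer rate. The figures cannot be multiplied together.

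The spectrum-bias sentence in the Discussion contrasts this design with prostatectomy-correlation studies, so it is undermined only if the men are in fact left out.

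**Conclusion.** The concern holds in this form. The stated reason for 299 treats men without a lesion as adding no pair, although they have a systematic result and are targeted-negative by definition. This goes beyond a detail left to a fuller document, because the enrolment figure rests on it. The section needs changing under either handling: if the men are left out, the tests lean towards targeted biopsy whenever s is more than negligible; if they are counted, the stated reason fails and the planning values must be shown to describe the whole cohort.

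The direction among discordant pairs is certain. The size is conditional on s, on 15% of men having no target for the regimen tested (the article does not tie that share to MRI, CEUS or both), and on where the 15% discordance applies. At s = 0 there is no inflation of the error rate. That the exclusion will take place is an inference from the sample size, not something the article states.

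**What to change.** **Statistical analysis section.** Define the primary analysis set as every man who had both imaging studies and the systematic biopsy. Count a man with no target for a modality as negative for that modality, and count him as negative for the combined regimen on this ground only if he has no target on either. Keep the comparison in men with a target as a labelled secondary analysis.

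**Sample size calculation section.** Keep 299, but drop the rationale that men without a lesion are lost to the comparison. Say which population the 15% discordance and the +5 points describe, and restate power for the whole cohort: about 85% if they describe all men, or the values in the second table with its assumed s if they describe only men with a lesion. Going back to 260 would be justified only in the first case.

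**Cost.** This is a change of wording, with no added procedures and no change to the planned enrolment. The downside is that the stated power may become less favourable. If the planned difference holds only in men with a lesion and s is not near zero, 299 men do not give 80% power, and the sponsor would have to state that openly or reconsider the size.

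### One 15% no-target allowance serves two separate tests: it is a lower bound on the loss in each, so 299 men leave at most 254 pairs, not the 260 required

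*Protocol article*

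**What the plan says.** All places are in the protocol article.

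- **Sample size calculation.** One paired non-inferiority comparison is sized, with a systematic detection rate of 45%, a margin of 1 percentage point, at most 15% discordant pairs, an expected difference of 5 points, alpha 5% and power 80%. The result is 260 men. A single allowance follows, because an estimated "15% of the patients that are scheduled for biopsies will not receive targeted biopsies due to the absence of PCa suspected lesions on imaging", and enrolment is set at 299.
- **Statistical analysis.** There are two single-technique tests, not one: "both targeted biopsy regimens will be tested separately for non-inferiority against current standard 12-core systematic biopsies", each "using a one sided non-inferiority test for correlated proportions". A combined-target analysis and direct McNemar comparisons of the three protocols are added.
- **Abstract (Methods/design) and Study design.** Targets for the two techniques are fixed by different readers, each blinded to the other technique. The abstract's wording lets a man have targets on one technique, on both, or on neither.

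The article gives no expected no-target share for MRI or for CEUS + CUDI. It also does not say how a man without a target on one technique enters that technique's test.

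**The concern.** A man who receives no targeted biopsies has no target on MRI and none on CEUS + CUDI. The share of such men cannot exceed the no-target share of either technique alone. The MRI test would also lose men who have only a CEUS target, and the CEUS test would lose men who have only an MRI target. The two shares are equal only if both techniques are blank in exactly the same men. The plan does not assume that, since it sets out to study how far the techniques complement each other.

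The allowance therefore measures a different quantity from the one each test needs. At stake are the 260 pairs and the 80% power, which the reader will attach to each of the two non-inferiority tests. On the same logic, the direct MRI-versus-CEUS comparison would have fewer pairs still.

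**Working it through.** **Inputs.** From Sample size calculation: difference d = 0.05 in favour of targeted biopsy, margin m = 0.01, discordance ψ = 0.15, alpha 0.05, power 0.80, allowance 15%, enrolment 299. From Statistical analysis: the test is one-sided and paired.

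**1. Reproduce 260.** The paired score test gives

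n = [(1.645·√V0 + 0.842·√V1) / (d + m)]²

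with V1 = ψ − d² = 0.15 − 0.0025 = 0.1475 and V0 = 0.1532, the variance restricted to a difference of −0.01. Then

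n = [(1.645 × 0.3914 + 0.842 × 0.3841) / 0.06]² = 259.8, i.e. 260.

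The plan's figure is reproduced. The simpler Wald form gives 253.3. One-sided 2.5% gives 322 to 330 and does not fit.

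**2. Reproduce 299.** 260 × 1.15 = 299. To keep 260 after losing 15%, the calculation is 260 / 0.85 = 305.9, i.e. 306.

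**3. The floor for each test.** If 15% have no target on either technique, each test loses at least 15%, so 299 × 0.85 = 254.15, at most 254 pairs. If 15% was meant as the rate for each technique, the result is again 254. Enrolling 299 delivers 260 only if the loss is at most 39 / 299 = 13.0%.

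Power at 254 pairs, with Φ the standard normal distribution function:
- Score: Φ[(0.06·√254 − 1.645·√0.1532) / √0.1475] = 79.2%
- Wald: Φ[0.06·√254 / √0.1475 − 1.645] = 80.1%

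**4. Beyond the floor (illustration only).** Assume that both techniques have the same no-target share q, that 15% are negative on both, and that the 5-point difference and 15% discordance are unchanged among the men who remain. With correlation φ between the two negatives, q solves q² + φ·q(1 − q) = 0.15.

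| φ | q | Pairs, 299 enrolled | Power, score / Wald | Pairs, 306 enrolled |
|---|---|---|---|---|
| 1 | 15.0% | 254 | 79.2% / 80.1% | 260 |
| 0.75 | 18.8% | 243 | 77.6% / 78.5% | 248 |
| 0.5 | 24.2% | 227 | 75.1% / 76.1% | 232 |
| 0 | 38.7% | 183 | 66.9% / 68.0% | 187 |

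The last column shows that correcting the inflation to 306 cures the shortfall only when the same men are target-free on both techniques.

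Men with targets on both techniques number 299 × (1 − 2q + 0.15): about 199 at φ = 0.5 and 112 at φ = 0.

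**5. If no-target men count as targeted-negative.** All 299 pairs stay, but the difference shrinks. Take 15% no-target men of whom a share r is positive on systematic biopsy (r is assumed), and the planned rates in the other 85%. Targeted-only positives are 0.85 × 0.10 = 0.085. Systematic-only positives are 0.85 × 0.05 + 0.15r.
- r = 10%: difference 0.085 − 0.0575 = 2.75 points, discordance 14.25%, power about 52%
- r = 20%: difference 0.085 − 0.0725 = 1.25 points, discordance 15.75%, power about 25%

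**The case against.** **The 15% may be a per-technique rate.** The sizing paragraph treats targeted biopsy generically, with one difference, one discordance rate and one allowance, and it does not spell out that the 15% means neither technique. This stands as a caveat. On that reading there is no mismatch between the allowance and the tests, only unclear wording, but 299 still leaves 254 pairs.

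**The certain shortfall is an inflation slip.** This also stands. The 6 missing pairs come from multiplying by 1.15, and with 306 enrolled the floor case reaches 260. What the separate tests add is only the loss beyond 15%.

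**Power may still be 80% at the floor.** By the Wald formula it is 80.1%. By the score formula that reproduces 260 it is 79.2%. So one cannot say that the stated power is clearly missed at the floor; only the pair count is certainly missed.

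**The larger losses rest on assumptions.** A reader might infer from the table that each test has only about 68% power. The article does not support that. The figure needs equal no-target shares and statistically independent negatives, which is unlikely when both techniques look for the same disease in the same prostate. It also keeps the difference and discordance fixed in a selected subset.

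**No exclusion rule is stated.** The article compares per-patient rates of whole regimens and claims to study the relevant biopsy population. If a no-target man counts as targeted-negative, no pair is lost. But the allowance then has no purpose, and the expected difference has to be reconsidered.

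**Conclusion.** The point holds in a limited form. The plan makes one allowance for two separate tests, and on its own exclusion logic that allowance is the minimum loss in each. Enrolling 299 delivers at most 254 pairs per test, 6 short of 260, on either reading of the 15%. The cost at that minimum is about 1 point of power or less.

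Any man with a target on one technique only adds to the loss in the other test, and enrolling 306 would not remove that. The article gives no per-technique share, so the size of the extra loss is unknown. The range from about 78% power (correlation 0.75) to 67–68% (independence) is illustrative. It would be wrong to infer that the trial is shown to be badly underpowered, or that the 15% certainly means men blank on both techniques.

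The conclusion assumes that men without a target drop out of that technique's test, which the allowance implies but no analysis rule states.

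**What to change.** In Sample size calculation, replace the single 15% with an expected no-target share for MRI and another for CEUS + CUDI, or state that 15% is the rate for each technique. Then restate the evaluable pairs and power for each of the two tests at 299 enrolled.

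If men without a target are instead to be counted as targeted-negative, say so, drop the allowance, and restate power with the difference and discordance expected across all enrolled men.

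The cost is two numbers and a restated power for each comparison. No extra men are needed if a slightly less favourable power is accepted. Keeping 260 pairs would require 260 / (1 − L) men, with L the larger of the two shares: 306 at 15%, 325 at 20% and 347 at 25% (the last two shares are assumed).
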